### **9.9.2 Dose Regimen (DR) escalation rules**

A subject will be considered DR escalation-evaluable if they are evaluable for MTDR DLT and are counted as part of a 3-subject dose escalation Cohort according to the rules described below.

The following rules will be applied separately and independently for each Arm. DLTs are defined in Section 5.2.

*Dose escalation rules using a modified 3 + 3 design for Arms A, B, and C.* DRs are detailed in Section 5.1.3.

1. Escalation and de-escalation decisions will use cohorts of 3 consecutive toxicity-evaluable subjects treated at the same DR
2. The dose escalation route will be similar to a 3+3 design, and will allow expansion on the tentative MTDR if 1 DLTs out of the first cohort of 3 and 1 DLTs out of the second cohort of 3 were observed
  - a. If 0 DLTs out of the first cohort of 3 (0/3) within a DR, and there is a DR available for escalation, it will escalate to the next DR. If there is no DR

available for escalation, then this DR is considered as tentative MTDR and another cohort of 3 will be treated at the current DR.

- b. If 1 DLTs out of the first cohort of 3 (1/3), a second cohort of 3 will be treated and evaluated at the current DR
  - i. If 0 DLTs out of the second 3 and there is a DR available for escalation, it will escalate to the next DR. If there is no DR available for escalation (1 DLT in first 6), the MTDR will be estimated
  - ii. If 1 DLTs out of the second cohort of 3 (i.e. 2 DLT in the first 6), a third cohort of 3 will be treated at the current DR. If there are 0 DLTs in the third cohort of 3, the MTDR will be estimated. If there is 1 DLT in the third cohort (i.e. 3 DLTs in the first 9), a final cohort of 3 will be treated at the current DR and the MTDR will be estimated once all subjects have been evaluated.
- c. If 2 or more DLTs out of any cohort of 3 ( $\geq 2/3$ ) toxicity-evaluable subjects, the current DR will be shut down and the DR will de-escalate to the previous DR. If the first 2 subjects of any cohort of 3 both experience DLTs and the third subject has not received CAR T cells, stop the cohort at 2 subjects and de-escalate to previous DR and the third subject will become the first subject of a new cohort. If there is no DR available for de-escalation (lowest), the arm will be shut down.
- d. After de-escalation, if the current DR has fewer than 6 toxicity-evaluable subjects, then the requisite number of subjects will be treated and evaluated at that DR and the MTDR will be re-estimated. If the current DR has 6 or more than 6 toxicity-evaluable subjects, MTDR will be estimated.

### 9.9.3 Stopping rules

In the event of the following, further T cell infusions will be suspended pending review by the DSMB and consultation with the FDA:

- Death unrelated to disease progression or accidental trauma that occurs within 30 days of CAR T cell administration

To further protect the safety of patients, infusions will also be suspended pending review by the DSMB and consultation with the FDA if the lower bound of a 1-sided 80% exact binomial confidence interval of the discontinuation rate due to medically significant Grade 4 or greater events that are possibly, probably, or definitely attributable to CAR T cells is  $> 10\%$ .

Operationally, any of the following would trigger such a rule: 2 out of the first  $\leq 5$  subjects or 3 out of the first  $\leq 11$  patients or 4 out of the first  $\leq 18$  patients or 5 out of the first  $\leq 24$  have unacceptable toxicity or  $\geq$  Grade 4 AEs that are possible, probably, or definitely attributable to CAR T cells. If the true probability of  $\geq$  Grade 4 AE is 2.5%, the probability of study suspension under the above rule is approximately 0.007; if the true probability is 30%, the probability of suspension is approximately 0.93 (probabilities estimated from 5,000 simulations).

This rule will apply to medically significant (requiring medical intervention)  $\geq$  Grade 4 toxicities that are possibly, probably, or definitely attributable to CAR T cells, with the exception of Grade 4 CRS for  $< 72$  hours, and Grade 4 fever.

If this rule is met, further T cell infusions for all subjects enrolled will be immediately halted. A safety evaluation will be performed and reviewed with the FDA and DSMB prior to resuming any CAR T cell infusions.

Additionally, the Study Chair may shut down a DR at any time due to toxicities observed or efficacy observed at lower DRs.

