## 9 STATISTICAL CONSIDERATIONS

### 9.1 Accrual and Study Duration

Up to 90 patients will be enrolled into BrainChild-03 at Seattle Children's Hospital. Anticipated duration of enrollment accrual is 6 years. Anticipated duration of the active treatment portion of the study is up to 7 months, and anticipated duration of the long-term follow-up period is 15 years.

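### The Grade 4+ suspension counts (2/5, 3/11, 4/18, 5/24) follow a 1-sided 90% bound, not the stated 80%, and end at 24 of up to 90 subjects

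*Protocol*

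**What the plan says.** Protocol Section 9.9.3 defines a trial-wide safety rule. Infusions stop, pending DSMB review and FDA consultation, once a confidence bound exceeds 10%. The bound is "the lower bound of a 1-sided 80% exact binomial confidence interval of the discontinuation rate due to medically significant Grade 4 or greater events", counting those judged at least possibly attributable to the CAR T cells.

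The section then turns this into counts: "Operationally, any of the following would trigger such a rule: 2 out of the first" 5 or fewer subjects, 3 of the first 11 or fewer, 4 of the first 18 or fewer, or 5 of the first 24 or fewer. No count is given beyond 24.

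Two operating characteristics follow. At a true Grade 4+ rate of 2.5%, "the probability of study suspension under the above rule is approximately 0.007". At 30%, "the probability of suspension is approximately 0.93 (probabilities estimated from 5,000 simulations").

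A met rule halts infusions for every enrolled subject, so it pools all arms and dose regimens. Section 9.1 sets the scale: "Up to 90 patients will be enrolled into BrainChild-03".

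**The concern.** The confidence-bound sentence and the list of counts are presented as the same rule, but they give different halt decisions. The difference runs in the less protective direction: every listed count meets the stated bound, but the list leaves out many counts that also meet it. Someone working from the list would not suspend at counts where the sentence above it requires suspension. The DSMB and FDA are shown suspension probabilities that the stated bound does not have.

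The list also stops at 24 subjects in a trial that may enrol up to 90.

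A smaller point is that the event changes within the section. It is first a discontinuation rate due to Grade 4+ events, then unacceptable toxicity (not defined) or attributable Grade 4+ adverse events, then medically significant Grade 4+ toxicities with exceptions for CRS and fever.

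**Working it through.** **Inputs.** From Section 9.9.3: 1-sided 80% exact binomial bound; threshold 10%; counts 2/≤5, 3/≤11, 4/≤18, 5/≤24; quoted suspension probabilities 0.007 (true rate 2.5%) and 0.93 (true rate 30%) from 5,000 simulations. From Section 9.1: up to 90 subjects.

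**Formula.** For x events in n subjects, the exact 1-sided lower bound at confidence c is the (1 − c) quantile of Beta(x, n − x + 1). It exceeds 10% exactly when P(X ≥ x | n, 0.10) < 1 − c. For each x, the boundary is the largest n that meets this condition.

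**Step 1: the plan's own probabilities.** An exact recursion over subjects, checking after each one, applied to the listed counts up to n = 24 gives 0.0077 at 2.5% and 0.924 at 30%. The simulation standard errors for 5,000 runs are √(0.0077 × 0.9923 / 5000) ≈ 0.001 and √(0.924 × 0.076 / 5000) ≈ 0.004. The quoted 0.007 and 0.93 are therefore consistent with the list over 24 subjects.

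**Step 2: the boundary of the stated bound.**

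| Events | Largest n at 1-sided 80% (bound there; at n + 1) | Largest n at 1-sided 90% (bound there) | Listed n |
|---|---|---|---|
| 1 | 2 (10.6%; 7.2%) | none | not listed |
| 2 | 8 (10.4%; 9.3%) | 5 (11.2%) | 5 |
| 3 | 15 (10.4%; 9.8%) | 11 (10.5%) | 11 |
| 4 | 23 (10.15%; 9.7%) | 18 (10.06%) | 18 |
| 5 | 31 (10.1%; 9.8%) | 25 (10.06%) | 24 |

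At a true rate of 10%, the tail probabilities at the four listed counts are 0.081, 0.090, 0.098 and 0.085. All lie just below 0.10, as a 90% rule would produce, and well below 0.20. The one departure from the 90% boundary is 5/24 instead of 5/25, which fits a cut-off at 24 subjects. Other interval methods at 1-sided 80% do not give the list either: Wilson 2/11, 3/18, 4/26, 5/35; Wald 2/9, 3/16, 4/24, 5/32; Jeffreys 2/11, 3/19, 4/27, 5/35.

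**Step 3: where the two rules disagree.** The stated bound requires suspension and the list does not at 1 event in 1–2 subjects, 2 in 6–8, 3 in 12–15, 4 in 19–23 and 5 in 25–31. At 2 of 6, for instance, the 80% lower bound is 14.0%.

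**Step 4: suspension probabilities by rule (same recursion).**

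| True rate | Listed counts, N = 24 | 80% rule without 1/≤2, N = 24 | 80% rule with 1/≤2, N = 24 | 90% rule, N = 90 |
|---|---|---|---|---|
| 2.5% | 0.008 | 0.019 | 0.060 | 0.008 |
| 10% | 0.18 | 0.31 | 0.38 | 0.29 |
| 20% | 0.65 | 0.78 | 0.81 | 0.957 |
| 30% | 0.92 | 0.96 | 0.97 | 1.000 |

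The listed counts cannot trigger after subject 24. Their column is unchanged however many subjects are treated: at a true rate of 20% it stays at 0.65, against 0.957 for the 90% boundary carried to 90.

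**The case against.** The strongest reply is that only a label is wrong. The counts and both quoted probabilities agree with each other, and the reference to the rule above most naturally means the list. If the level had been written as 1-sided 90%, or as a two-sided 80% interval with 10% in each tail, everything up to subject 24 would be consistent apart from 5/24 against 5/25. This is a fair reading of how the error arose. It shows that the probabilities are right for the list; it does not make them right for the bound as written.

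A second reply is that the bound sentence has no subject limit, so a rule still applies after subject 24, and that the list gives sufficient triggers, not exhaustive ones. Both are true in form: at the 80% level the listed counts have bounds of 16.9%, 14.3%, 13.0% and 13.1%. But the list is introduced as the operational form of the rule, and the quoted probabilities treat it as complete.

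Third, other safeguards continue: suspension for a non-progression, non-accidental death within 30 days, per-arm DLT rules, the 33% DLT check in the expansion cohorts, weekly safety review and DSMB review about every 6 months. They cover other events or thresholds, and none replaces a pooled 10% Grade 4+ limit.

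Two qualifications stand. Ninety is an enrolment ceiling, and subjects who never receive product cannot contribute an event, so the 90 − 24 = 66 subjects without a listed count are an upper limit. The event-wording point is minor, because a later paragraph of the same section states the scope and the exceptions.

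**Conclusion.** The concern holds. The stated level, the listed counts and the quoted probabilities cannot all be correct: the counts are a 1-sided 90% boundary cut at 24 subjects, and the probabilities belong to those counts. Against the bound as written, the list understates the chance of suspension within 24 subjects by 0.12 to 0.20 at a true rate of 10% (0.18 against 0.31 to 0.38) and by 0.13 to 0.16 at 20% (0.65 against 0.78 to 0.81). At 30% the gap is smaller, 0.92 against 0.96 to 0.97.

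The lower end of each range leaves out the trigger of 1 event in the first 2 subjects, which the 80% bound strictly implies but which may not have been intended. The figures assume independent subjects with a common event rate and a check after every subject. That 24 was a planning horizon is an inference; the protocol does not say so. Because two readers of Section 9.9.3 could reach opposite halt decisions on the same data, in a trial that enrols children from age 1, this must be fixed.

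**What to change.** The sponsor and DSMB should decide which level was intended and make Section 9.9.3 agree with it throughout.

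- **Option (a), which the counts and probabilities point to:** restate the level as 1-sided 90% and list 2/≤5, 3/≤11, 4/≤18, 5/≤25, 6/≤32, 7/≤40, 8/≤47, 9/≤55, 10/≤63, 11/≤71, 12/≤79, 13/≤88, 14/≤90. Over 90 subjects the suspension probability is 0.008 at a true rate of 2.5%, 0.29 at 10%, 0.957 at 20% and 1.000 (rounded) at 30%.
- **Option (b):** keep 1-sided 80% and list 1/≤2, 2/≤8, 3/≤15, 4/≤23, 5/≤31, 6/≤39, 7/≤47, 8/≤56, 9/≤65, 10/≤73, 11/≤82, 12/≤90. Say explicitly whether 1/≤2 applies. At a true rate of 2.5% over 90 subjects, the suspension probability is 0.061 with that trigger and 0.019 without it.

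In either case, state the number of treated subjects to which the quoted probabilities refer, and use one event definition in every sentence, with unacceptable toxicity either defined or removed.

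The cost is wording in Section 9.9.3, matching text in the DSMB charter and a short recalculation. No extra patients are needed. Option (b) would also bring more suspensions when the true rate is low.

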#### **9.9.4 Definition and determination of MTDR and RP2DR**

The MTDR is defined as the highest DR with at least six DLT-evaluable subjects, whose cumulative DLT rate during Courses 1 and 2 is below 34%. The MTDR will be estimated separately for each Arm.

Per investigator discretion and with DSMB approval, if a DR lower than the selected MTDR displays satisfactory disease response and has at least six DLT-evaluable subjects, then this DR can be chosen as the RP2DR instead of the MTDR.

#### **9.10 Expansion Cohort**

Following determination of the safety and toxicity of each arm based on our modified 3+3 design, an expansion cohort of up to 12 subjects in each arm will be started with treatment at the MTDR/RP2DR. The purpose of the expansion cohort is to provide a more precise assessment of the tolerability and toxicity of this treatment when dose at the MTDR/RP2DR as well as gain additional knowledge regarding secondary and exploratory objectives with particular focus on the duration and magnitude of in vivo persistence of CAR T cells in the cerebral spinal fluid including descriptions of cellular and protein components.

The expansion cohort will begin once the MTDR/RP2DR has been determined. For the expansion cohort, up to 12 additional subjects will be treated. Accrual to the expansion cohort will be continuous and will not depend upon the completion of treatment of the previous patients in the expansion cohort. Ongoing safety monitoring will occur during the expansion cohort with analysis in combination with all subjects treated at the MTDR/RP2DR. If at any time the DLT rate appears to exceed 33%, infusions would be halted to allow review with the Data Safety Monitoring Board (DSMB). Examples include a DLT rate of 3/7-9, 4/10-12, 5/13-15, 6/16-18, or 7/19-21.

#### **9.11 Safety Monitoring**

##### **9.11.1 Weekly safety review**

The Study Chair, Investigators, study statistician (if needed), CRAs, research nurses, and other site and Sponsor staff will meet weekly (or as needed when there are active subjects) to review subject enrollment and conduct subject safety review. This group is responsible for monitoring

the data and safety of this study, including implementation of the stopping rules for dose escalation. During this meeting, this group will review as applicable enrollment, AEs, DLTs, and protocol compliance, CAR T cell persistence analysis, feasibility data and follow-up information for each subject.

### **9.11.2 Data Safety Monitoring Board**

The study will be monitored by a DSMB. This is an independent committee with no affiliation to the protocol. The DSMB will meet prior to the study opening to review and approve the study protocol and DSMB Charter. The DSMB will review toxicity data approximately every 6 months. In addition, the DSMB will review study conduct including accrual, drop-outs, data completeness, any inability to generate CAR T cell product that meets all Quality Control criteria, positive bacterial cultures from the CAR T cell product, subjects not meeting eligibility criteria for CAR T cell infusion after enrollment, protocol compliance, and treatment efficacy measures.

DSMB meetings may be called at any time by the DSMB chair or sponsor for additional safety review if indicated. Following any temporary suspension of accrual for a safety event, the DSMB will be convened and will further review the safety data to determine if continuation of accrual is appropriate. Applicable regulatory agencies will receive copies of the DSMB's recommendations as they become available.

## **10 DISEASE RESPONSE**

### **10.1 Disease Response Criteria**

#### **10.1.1 Measurable disease**

Measurable disease is defined as a lesion that is at minimum 10 mm in 2 dimensions on standard MRI.

#### **10.1.2 Evaluable disease**

Evaluable disease is defined as a lesion or multiple lesions, with no lesion that can be accurately measured in at least 2 dimensions and does not meet criteria to be measurable. Such lesions may be evaluable by pathology, MRI, immunocytochemistry techniques, tumor markers, CSF cytology, or other reliable measures.

#### **10.1.3 Selection of target and non-target lesions**

For most CNS tumors, only 1 lesion/mass is present and therefore is considered a “target” for measurement/follow up to assess for tumor progression/response. If multiple measurable lesions are present, up to 5 may be selected as target lesions. Target lesions should be selected on the basis of size and suitability for accurate repeated measurements. All other lesions will be followed as non-target lesions. The lower size limit of the target lesion(s) should be at least twice the thickness of the slices showing the tumor to decrease the partial volume effect (e.g., 8 mm lesion for a 4-mm slice).

The presence of non-target lesions should be noted.

#### **10.1.4 Response criteria for target lesions**

*Complete Response (CR)*: Disappearance of all target lesions

*Partial Response (PR)*:  $\geq 50\%$  decrease in the sum of the products of the two perpendicular diameters of all target lesions (taking as reference the initial baseline measurements)

*Stable Disease (SD)*: Neither sufficient decrease in the sum of all target lesions to qualify for PR, nor sufficient increase to qualify for progressive disease

*Progressive Disease (PD)*:  $\geq 25\%$  increase in the sum of the products of the perpendicular diameters of the target lesions (taking as reference the smallest sum of the products observed since the start of treatment)

*Immune-Related Progressive Disease (irPD)* may occur in the setting of CAR T cell therapy and can manifest as increased disease and/or new lesions and is distinct from PD [93]. irPD will be documented as SD. irPD must occur within 6 months of the initiation of immunotherapy, cannot last longer than 6 months, and cannot correspond to neurologic decline that is definitely attributable to worsening disease. If irPD is suspected:

- Re-imaging is recommended in 3 months and if progressive disease is confirmed, subject will be determined to have PD
- Biopsy should be considered and if pathology is consistent with progressive disease, subject will be determined to have PD

#### 10.1.5 Response criteria for non-target lesions

*Complete Response (CR)*: Disappearance of all non-target lesions

*Stable Disease (SD)*: The persistence of one or more non-target lesions

*Progressive Disease (PD)*: The appearance of one or more new lesions and/or unequivocal progression of existing non-target lesions

*Immune-Related Progressive Disease (irPD)* may occur in the setting of CAR T cell therapy and can manifest as increased disease and/or new lesions and is distinct from PD [93]. irPD will be documented as SD. irPD must occur within 6 months of the initiation of immunotherapy, cannot last longer than 6 months, and cannot correspond to neurologic decline that is definitely attributable to worsening disease. If irPD is suspected:

- Re-imaging is recommended in 3 months and if progressive disease is confirmed, subject will be determined to have PD
- Biopsy should be considered and if pathology is consistent with progressive disease, subject will be determined to have PD

#### 10.1.6 Evaluation of best overall response

The overall response assessment takes into account response in both target and non-target lesions and the appearance of new lesions, according to the criteria described in the table below. The best overall response is the best response recorded from the start of the treatment until disease progression/recurrence (taking as reference for PD the smallest measurements recorded since the treatment started). In general, the subject's best response assignment will depend on the achievement of both measurement and confirmation criteria.

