- If the subject is receiving corticosteroids for symptomatic relief from their CNS disease, steroid dosing must be stable or decreasing for ≥ 1 week with a maximum dexamethasone dose of 2.5 mg/m^2/day on the day of the infusion. Corticosteroid physiologic replacement therapy for management of pituitary/adrenal axis insufficiency and/or topical administration (e.g., inhaled or dermatologic) is allowed.
- Subject must have adequate organ function as indicated by:
  - Renal: Serum creatinine ≤ ULN per Table 3-2 Screening Serum Creatinine Values
  - Hepatic: Total bilirubin < 3 times ULN for age OR conjugated bilirubin < 2 mg/dL
  - Respiratory: Oxygen saturation ≥ 90% on room air without supplemental oxygen or mechanical ventilation, and no dyspnea at rest
  - Hematologic: Platelets ≥ 100,000/μL (transfusion(s) allowed to meet criteria)
- No evidence of clinically significant progressive encephalopathy or uncontrolled seizure activity.
- Subject is taking an anti-seizure medication.
- No evidence of active severe infection, defined as: 1) positive blood culture within 48 hours of CAR T cell infusion; or 2) fever > 38.2°C AND clinical evidence of infection within 48 hours of CAR T cell infusion

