### **5.5.2 Requirements for subsequent CAR T cell infusion and dose modification**

The following criteria must be met prior to administration of subsequent CAR T cell product:

- No DLT (Section 5.2) has occurred following infusion of CAR T cell (See Section 8 Removal from Protocol Therapy & Off Study Criteria).
- Cryopreserved CAR T cells are available and released for infusion
- Subject must have adequate organ function as indicated by:
  - Renal: Serum creatinine  $\leq$  ULN per Table 3-2
  - Hepatic: Total bilirubin  $< 3$  times ULN for age OR conjugated bilirubin  $< 2$  mg/dL
  - Respiratory: Oxygen saturation  $\geq 90\%$  on room air without supplemental oxygen or mechanical ventilation, and no dyspnea at rest
  - Hematologic: Platelets  $\geq 100,000/\mu\text{L}$  (transfusion(s) allowed to meet criteria)
- No evidence of clinically significant progressive encephalopathy or uncontrolled seizure activity
- Subject is taking an anti-seizure medication
- No evidence of active severe infection, defined as: 1) positive blood culture within 48 hours of CAR T cell infusion; or 2) fever  $> 38.2^{\circ}\text{C}$  AND clinical evidence of infection within 48 hours of CAR T cell infusion
- Subject has a CNS reservoir catheter in place
- Subject is not breastfeeding
- Female subjects of childbearing potential only: subject has a negative pregnancy test within 2 days prior to Week 1 CAR T cell infusion of each Course

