## **8 REMOVAL FROM PROTOCOL THERAPY & OFF STUDY CRITERIA**

### **8.1 Removal from Protocol Therapy**

A subject may be discontinued from protocol therapy at any time. Subjects will be removed from protocol therapy for the following reasons:

- Subject/family or the investigator feels that it is not in the subject's best interest to continue
- Subject/family is non-compliant with protocol therapy and/or clinic appointments
- Subject receives medical intervention prohibited under this protocol or which will interfere with the ability to assess toxicity or response following CAR T cell infusion
- Subject experiences a DLT following CAR T cell infusion
- Subject does not meet criteria to receive the next CAR T cell infusion as defined in Section 5.5.2
- Subject is pregnant
- Subject meets criteria for removal from study (Section 8.2)

All subjects who discontinue protocol therapy should come in for an End of Therapy/Early Discontinuation Visit per Appendix 2 – Schedule of Procedures and should be encouraged to complete all remaining scheduled visits and procedures.

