**Table 10-1 Best Overall Response**

| Target lesions | Non-Target lesions | New Lesions | Overall response |
|----------------|--------------------|-------------|------------------|
| CR             | CR                 | No          | CR               |
| CR             | SD                 | No          | PR               |
| PR             | CR or SD           | No          | PR               |
| SD             | CR or SD           | No          | SD               |
| PD             | Any                | Yes or No   | PD               |
| Any            | PD                 | Yes or No   | PD               |
| Any            | Any                | Yes         | PD               |

Subjects with a global deterioration of health status requiring discontinuation of treatment without objective evidence of disease progression at that time should be classified as having

“symptomatic deterioration.” Every effort should be made to document the objective progression even after discontinuation of treatment.

In some circumstances, it may be difficult to distinguish residual disease from normal tissue. When the evaluation of complete response depends on this determination, it is recommended that the residual lesion be investigated (biopsy) to confirm the complete response status.

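### CR and PR are credited with no condition on concurrent bevacizumab or raised dexamethasone, both allowed on treatment, and best response does not end at non-protocol anti-tumour therapy

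*Protocol*

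**What the plan says.** **Scoring.** In Protocol Sections 10.1.4 and 10.1.5, CR and PR rest on the size, disappearance or persistence of lesions. Section 10.1.6 combines these: "The overall response assessment takes into account response in both target and non-target lesions and the appearance of new lesions". PD in target lesions is judged by "taking as reference the smallest sum of the products observed since the start of treatment". Section 10.1.6 adds that "best response assignment will depend on the achievement of both measurement and confirmation criteria", but Section 10.1 does not say what confirmation consists of. The advice below Table 10-1 that "it is recommended that the residual lesion be investigated (biopsy) to confirm the complete response status" concerns CR only.

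**Response window.** "The best overall response is the best response recorded from the start of the treatment until disease progression/recurrence". Section 9.3 measures response duration from the first CR or PR to documented treatment failure. Neither window stops when another anti-tumour therapy starts.

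**Drugs allowed on treatment.** Section 6.4 advises considering corticosteroids for neurologic changes of Grade 2 or higher, starting with dexamethasone 5-10 mg every 6 to 12 hours. It also permits bevacizumab by clinical judgment, with no arm limit. Table 6-3 gives Arm C up to two bevacizumab doses two weeks apart. Section 5.2 exempts from DLT an Arm C Grade 3 neurologic event that improves within 21 days, expressly including events treated with either drug; for Arms A and B the limit is 7 days.

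**Limits at infusion.** The first infusion requires 28 days off bevacizumab (Table 5-2) and stable or falling steroids "with a maximum dexamethasone dose of 2.5" mg/m²/day (Section 5.5.1). Section 5.5.2 opens with "The following criteria must be met prior to administration of subsequent CAR T cell product" and lists neither condition.

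**The concern.** A subject can have a neurologic event, receive bevacizumab or high-dose dexamethasone, incur no DLT, continue CAR T infusions and be scanned soon afterwards. If lesions are smaller on that scan, the rules credit a CR or PR to the CAR T cells. They give no means of separating a decrease under these drugs from one without them. The document itself groups bevacizumab with the anticancer agents to be stopped before enrollment (Section 3.2.1, item 7), and its washout in Table 5-2 is longer than that for cytotoxic chemotherapy (28 against 21 days).

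At stake are disease response, which is a secondary objective, and the Section 9.9.4 provision that lets a DR below the MTDR become the RP2DR because of its disease response, with as few as six DLT-evaluable subjects.

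**Working it through.** The protocol states no response rate or sample size for response, so there is no figure to reproduce. The check compares the sections and then does simple arithmetic.

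**1. Where the drug limits apply**

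| | First infusion (5.5.1, Table 5-2) | Later infusions (5.5.2) | Baseline scan (9.8) | Response scan (7.18.1, 10.1) |
|---|---|---|---|---|
| Bevacizumab-free interval | 28 days | none listed | none | none |
| Dexamethasone cap | 2.5 mg/m²/day | none listed | none | none |

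The limits attach to the first infusion only, not to any scan.

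**2. Can a response scan fall soon after bevacizumab?** Undelayed Arm C: Course 1 Week 1 is Day 1, Course 1 Week 3 is Day 15, Course 2 Week 1 is Day 29 and Course 2 Week 3 is Day 43. Section 7.18.1 places the scan within a week of the last infusion (Days 43-50). Appendix 2, Table 1b, footnote i allows Week 4 ±3 days (Days 47-59). Both hold on Days 47-50. Assumed: first dose 2 days after the triggering infusion (range 1-4), second dose 14 days later.

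| Triggering infusion | Latest dose before scan | Days from dose to scan (range) |
|---|---|---|
| Course 1 Week 1 | Day 17 | 30-33 (28-34) |
| Course 1 Week 3 | Day 31 | 16-19 (14-20) |
| Course 2 Week 1 | Day 45 (second) | 2-5 (0-6) |
| Course 2 Week 3 | Day 45 (first) | 2-5 (0-6) |

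Only the earliest trigger clears 28 days. If the scan is put off four weeks (Day 43 + 28 = 71, or Day 50 + 28 = 78), a Course 2 Week 1 trigger gives 71 − 45 = 26 or 78 − 45 = 33 days. A Course 2 Week 3 trigger, with its second dose on Day 59, gives 12 or 19. For a subject removed after the trigger, the end-of-therapy MRI is due within 28 days of the final infusion, so at most 28 − 2 = 26 days after a single dose.

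**3. Dexamethasone.** The starting range is 5 mg × 2 = 10 to 10 mg × 4 = 40 mg/day. The first-infusion cap, at an assumed body surface of 0.5-2.0 m², is 2.5 × 0.5 = 1.25 to 2.5 × 2.0 = 5 mg/day. The dose still being taken on the scan day is unknown.

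**4. How much further decrease makes a PR?** After a CAR T decrease of fraction x, the extra proportional decrease needed is 1 − 0.5/(1 − x). For x = 0, 0.2 and 0.4 this is 50%, 37.5% and 16.7%. The other drug need not halve the lesion by itself.

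**5. The baseline can be affected too.** Section 5.4 allows bridging therapy. Bevacizumab need stop only 28 days before infusion, and Section 9.8 accepts a baseline evaluation up to 28 days before infusion. A baseline scan on the earliest permitted day can coincide with the last dose. If it read 80 where a drug-free scan would read 100 (assumed), PR would need 0.5 × 80 = 40 instead of 50. That pushes the response rate down.

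**6. PD reference.** PD starts at 1.25 × the smallest sum. With baseline 100, a drug-affected 60 puts PD at 75; any such minimum below 80 puts it below baseline (1.25 × 80 = 100).

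**7. Leverage on the rate.** One PR is 1/6 = 16.7 points at six subjects and 1/18 = 5.6 points at 6 + 12 expansion subjects. If 10-40% of subjects were scanned under these drugs and 10-50% of those became PR because of them, the gross upward effect would be 0.1 × 0.1 = 1 to 0.4 × 0.5 = 20 points. Both inputs are assumed, and step 5 is not netted off.

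**The case against.** - **No stated effect on lesion size.** The protocol nowhere says that bevacizumab or dexamethasone shrinks the measured area, and for dexamethasone it offers not even a hint. This stands. What the text shows is an attribution that cannot be resolved, not a proven shrinkage.
- **Direction.** A reader might infer that the response rate is biased upward. The documents do not support that, because the baseline scan can lie close to a bridging bevacizumab dose and the steroid cap is not tied to that scan.
- **Existing safeguards.** Section 8.1 removes a subject for an intervention "which will interfere with the ability to assess toxicity or response following CAR T cell infusion". That ends therapy but does not say how the scan counts, and these drugs are expressly permitted. Section 9.8 characterises response after Course 2 and later Courses, so a subject removed in Course 1 may contribute no scored response; this limits the removal scenario. Confirmation criteria are named and could be detailed in an SAP, but a repeat scan could fall under the same drugs.
- **Early PD.** A reader might also infer that a drug-lowered minimum will bring PD forward. Sections 10.1.4 and 10.1.5 allow growth within 6 months of starting immunotherapy to be recorded as SD when irPD is suspected, which partly buffers this.
- **Genuine activity.** Section 6.2 links neurologic changes to tumour inflammation, so treated subjects may include true responders. This stands, and it argues against rescoring their responses as SD.
- **End of window at new therapy.** Section 5.7.4 bars most other anti-tumour treatment until removal from therapy or 28 days after the final infusion, whichever is earlier. The gap therefore matters mainly for end-of-therapy and later scans in subjects who stop without PD.

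**Conclusion.** The point holds as a gap in the response criteria. As written, a decrease seen under permitted bevacizumab or raised dexamethasone is credited to the CAR T cells, and best response runs on past the start of other anti-tumour therapy. In undelayed Arm C, under the dosing-day assumption above, bevacizumab for a Course 2 event puts the Course 2 scan 2-5 days after the latest dose.

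The size and net direction of the bias cannot be derived. How often the drugs are used, their effect on lesion area and the drug status at baseline are all missing. The firm figures are the leverage of one PR: 16.7 points at six subjects and 5.6 at eighteen. The 1-20 point range is an illustration only.

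The consequence is limited to secondary response-based endpoints and the discretionary, DSMB-approved choice in Section 9.9.4. DLT and MTDR do not depend on lesion response. Nor does the document support treating every affected response as false or rewriting the PD reference: on-treatment MRI is only as clinically indicated (Appendix 2, Table 1b, footnote k) and a removed subject has no required scan beyond 28 days. Either step could lose true responses or delay PD. The change is worth making because it is cheap and leaves treatment untouched.

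**What to change.** Amend Section 10.1.6, with matching words in Sections 9.3 and 9.9.4:

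1. At the baseline scan and each response scan, record the date of the last bevacizumab dose and the current dexamethasone dose.
2. Flag any CR or PR first seen within 28 days of bevacizumab, or on non-physiologic dexamethasone above the dose at the baseline scan. The 28 days is a working interval borrowed from Table 5-2, where it governs infusion and not imaging.
3. Report the response rate twice: with all scans, and with CR/PR counted only on unflagged scans.
4. Do not let a flagged CR or PR be the sole support for choosing a lower DR under Section 9.9.4.
5. End the best-response and response-duration windows at the first non-protocol anti-tumour therapy and record its start date. Bevacizumab given for toxicity under Section 6.4 does not end them.
6. Leave the PD reference as written, with at most a sensitivity analysis that excludes flagged scans.

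**Cost.** Protocol wording and two data items: drug status at scans and the start date of subsequent therapy. Section 7.8 already captures on-therapy drugs, but its period starts at the first infusion (apart from apheresis) and stops at removal from therapy, so it does not secure the baseline-scan dose or later treatment. There will be a second, possibly lower, response rate, because some genuine responses will be flagged; at six subjects each one so set aside lowers that rate by 16.7 points.
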